#### Procedure for unblinding if needed {17b}

N/a. This study is unblinded.

### Data collection and management

#### Plans for assessment and collection of outcomes {18a}

Data are collected through three primary modes: abstraction of eCHIS data, quantitative questionnaires with perinatal women, CHWs and supervisors, and qualitative interviews with CHWs and supervisors.

#### *eCHIS* data abstraction

eCHIS data, including task completion and SMS messaging, is extracted directly from the eCHIS server.

#### Quantitative questionnaires

Quantitative questionnaires are administered electronically to women, CHWs, and supervisors by study staff using the REDCap platform. Women complete questionnaires during study visits at the facility at enrollment in pregnancy and at 6 weeks postpartum (Table 2). At each visit, a standardized questionnaire is administered to record self-reported outcomes and sociodemographic and clinical characteristics that may be associated with them. Outcomes include timing of breastfeeding initiation, introduction of complementary foods, application of substances to the umbilical cord, knowledge of eight danger signs (not feeding, high temperature, low temperature, fast breathing, difficulty breathing, not moving, convulsions, and jaundice) [53], timing of first bath, attending facility-based care during illness episodes, and acceptability of CHV-NEO, using the AIM [48]. Associated demographic and clinical factors include maternal education, income, employment, parity, distance from home to clinic, intimate partner violence, depression symptoms, past healthcare experience, parental self-efficacy, and infant sex.

CHWs and supervisors complete questionnaires annually: at study launch, 1 year, and study close (Table 2). Questionnaires include outcomes as well as demographic and professional characteristics that may be associated with outcomes. Outcomes include acceptability of CHV-NEO, assessed using the AIM measure [48], and time spent on work duties in the prior 2 weeks. Characteristics that may be associated with outcomes include professional background, training, and experience and comfort with the eCHIS platform.

#### Qualitative interviews

We conduct individual semi-structured interviews with a sample of CHWs and supervisors at intervention sites 1 year after the study trial launch and at the trial close. Interview guides explore determinants of implementation success, comparing CHWs exhibiting low vs. high fidelity delivery of the intervention. Discussion guides are based on constructs from the consolidated framework for implementation research (CFIR), adapted for use in LMIC settings [54]. IDIs are conducted by a trained social scientist fluent in English, Swahili, and Luo and audio-recorded, transcribed verbatim, and translated into English.

#### Plans to promote participant retention and complete follow-up {18b}

A study staff member is stationed at each facility and is responsible for the recruitment and follow-up of participants. Participants who are 2 weeks late for their 6-week study visit are actively traced by phone call and home visit to maximize completeness of 6-week visit data. We successfully used this approach in previous RCTs [55]. Data from participants who discontinue the study will be included in the analysis up to the point of discontinuation.

#### Data management {19}

Abstracted data is collected through direct extraction from eCHIS via a secure web-based login. Data is extracted and stored on a secure University of Washington server with restricted access. Questionnaire data is collected using the REDCap online version. Personal identifying information and consent forms are stored in a separate REDCap project from study data. All REDCap projects require login and password information unique to individual study staff. Data collectors receive study-specific training on all questionnaires and surveys. A data manager reviews all new enrollments and survey entries daily using quality control reports within REDCap and confirms end-of-day enrollments and questionnaire numbers with data collectors.

#### Confidentiality {27}

Personal identifying information is only collected for the in-depth cohort, CHWs, and supervisors. Personal information is stored separately from study data. Data abstracted from eCHIS does not include client identifiers such as names or phone numbers. Data is only collected and accessed by study staff who have received human subjects and data protection training through a secure server.

#### Plans for collection, laboratory evaluation, and storage of biological specimens for genetic or molecular analysis in this trial/future use {33}

N/a. This study will not be collecting any biological specimens.

### Statistical methods

#### Statistical methods for primary and secondary outcomes {20a}

Statistical analysis approaches for each outcome are summarized in Table 1. Analysis of primary and secondary outcomes will be by intention-to-treat. If participants relocate between facilities in different intervention arms during the course of the study, the original assignment is used in the analysis. For analyses that include random effects at the CHW level, if a participant’s assigned CHW changes, their data is analyzed under the CHW under whose care they are for the longest proportion of follow-up time preceding outcome ascertainment. Analyses will be adjusted for any baseline characteristics that differ significantly between study arms.

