### Outcomes {12}

#### Clinical outcomes

Primary, secondary, and exploratory clinical outcomes are summarized in Table 1. The primary outcome is neonatal mortality, defined as the death of a live-born infant within 28 days of birth, based on routine data abstracted from eCHIS during the study period. Secondary outcomes are ascertained among the in-depth perinatal cohort who complete study questionnaires. Secondary outcomes were selected based on the intervention’s hypothesized mechanism of action (Fig. 2) and their importance as intermediate outcomes in neonatal survival. These include initiation of breastfeeding within the first hour of life (ascertained by maternal self-report at the 6-week postpartum study visit); application of substances to cord (ascertained by maternal self-report at the 6-week visit); maternal knowledge of neonatal danger signs (defined as the number of the eight neonatal danger signs correctly named at the 6-week visit); and appropriate care seeking (defined as the proportion of illness episodes with danger signs where the infant attended the clinic, based on maternal self-report at the 6-week visit). Exploratory clinical outcomes include mothers’ identification of danger signs in their infants (defined as the proportion of all infants whose mothers report they ever exhibited a danger sign at the 6-week visit); infant hospital admissions (based on maternal self-report); and neonatal care delays (defined as the proportion of neonatal deaths attributable to each delay in the three delays model, based on review of adverse event reports by nurses and physicians on the study team).

**Table 1 Tab1:** Trial outcomes

Outcome	Indicator	Source and timing	Statistical analysis
Primary clinical outcome			
Neonatal mortality	Death during the first 28 days of life	eCHIS routine data throughout 2 years of study implementation	GLMM (RE by facility and CHW) with Poisson link and survival time as offset
Secondary clinical outcomes			
Initiation of early breastfeeding	Breastfed in the first hour of life	Questionnaire at 6-week visit	GLMM (RE by facility and CHW) with Poisson link and robust SE
Appropriate cord care	Application of nothing or chlorhexidine to umbilical cord	Questionnaire at 6-week visit	GLMM (RE by facility and CHW) with Poisson link and robust SE
Appropriate thermal care	No bath in the first 24 h of life	Questionnaire at 6-week visit	GLMM (RE by facility and CHW) with Poisson link and robust SE

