### Sample size {14}

Our study is powered for primary and secondary clinical outcomes. The cluster-randomized trial includes 20 facility clusters, 10 interventions, and 10 controls. For ascertainment of our primary outcome of neonatal mortality, we will abstract outcomes from eCHIS on 7200 pregnancies ending in live births across the clusters. With this sample size, assuming *α* = 0.05, two-sided tests, 10% attrition, a conservative coefficient of variation of 0.25, and assuming unequal cluster sizes with an average cluster size 360, we have 80% power to detect a difference in neonatal mortality of 21.0 vs. 10.3 per 1000 live births [43]. For ascertainment of secondary outcomes, we will enroll 2000 pregnant clients in the in-depth perinatal cohort. With this sample size, assuming *α* = 0.05, two-sided tests, 10% attrition, coefficient of variation of 0.25, and unequal cluster sizes (ranging between 80 and 120 per cluster), we have 80% power to detect a difference in early initiation of breastfeeding, thermal care, and cord care of 50% vs. 72%. We expect the outcomes of appropriate care-seeking and knowledge of danger signs to be correlated so we will correct these analyses for multiple comparisons. Assuming a Bonferroni-adjusted *α* = 0.025, we will have 80% power to detect a difference between arms of 2.0 vs. 2.4 danger signs named and 0.5 vs. 0.9 appropriate clinic visits attended in the first 6 weeks [6, 37, 49, 50].

Service delivery and implementation outcomes are ascertained among the in-depth perinatal cohort as well as all CHWs and supervisors providing services over the 2-year period (estimated sample size 700 CHWs and 40 supervisors). Quantitative and qualitative analyses of implementation outcomes are intended to be exploratory; no formal hypothesis testing will be performed. We expect sample sizes for qualitative interviews will be sufficient to reach theoretical saturation of themes [51].

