### Assignment of interventions: allocation

#### Sequence generation {16a}, concealment mechanism {16b}, and implementation {16c}

Facility-level cluster randomization was conducted using a restricted randomization approach. Facilities were stratified into eight groups of two to six facilities, based on similar characteristics that may influence outcomes of interest, including facility level, patient volume, rural/urban designation, and services offered. Randomization was conducted through an interactive event using an online visual simulation of randomization [52]. A representative from each facility “spun” an online “wheel” to determine their order of assignment within stratified groups and a second wheel to determine final assignment within the randomization stratum.

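### Covariates for the primary and secondary analyses are picked by baseline significance tests, which leaves the model unfixed and gives up precision

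*Protocol article*

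**What the plan says.** The statistical methods section (item 20a) opens with "Analysis of primary and secondary outcomes will be by intention-to-treat" and ends with the covariate rule: "Analyses will be adjusted for any baseline characteristics that differ significantly between study arms". It exempts no outcome, and it gives no candidate list, test, threshold or level of testing.

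Table 1 gives the primary model as "GLMM (RE by facility and CHW) with Poisson link and survival time as offset". It names random effects, link and offset for the primary and secondary models, but no covariates, so the sentence in 20a is the only covariate rule.

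Four other places bear on it:

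- Sample size (item 14): "The cluster-randomized trial includes 20 facility clusters, 10 interventions, and 10 controls".
- Sequence generation (item 16a): "Facilities were stratified into eight groups of two to six facilities, based on similar characteristics that may influence outcomes of interest". The characteristics named there are facility level, patient volume, rural or urban designation, and services offered. The analysis text does not carry them into the model.
- Quantitative questionnaires (item 18a): "Associated demographic and clinical factors include maternal education, income, employment, parity, distance from home to clinic, intimate partner violence, depression symptoms, past healthcare experience", followed by parental self-efficacy and infant sex. That makes ten factors, collected in the in-depth cohort only and not designated as adjustment covariates.
- Blinding (item 17a): analysts have access to the assignment.

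**The concern.** Adjustment is worth making when a covariate predicts the outcome. The rule asks a different question, whether the arms differ on the covariate by more than a test allows. With few clusters the two come apart. A strong predictor can be clearly unbalanced without reaching significance, and a covariate of no prognostic value can be selected by chance. Factors balanced by stratification are the least likely to be selected, although they were chosen because they may influence outcomes.

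This is not detail left to an analysis plan. The article states a rule, and an analysis plan that named covariates would have to depart from it. What is at stake is the precision of the primary and secondary comparisons, and whether a reader can know the model before the data are seen.

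**Working it through.** **The plan's own figure, for context.** Inputs from Sample size (item 14): rates 0.0210 and 0.0103, 10 clusters per arm, 360 × 0.9 = 324 per cluster after attrition, coefficient of variation 0.25, two-sided 5%.

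- Variance per cluster pair: [0.0210 × 0.9790 + 0.0103 × 0.9897]/324 + 0.25² × (0.0210² + 0.0103²) = 0.0000949 + 0.0000342 = 0.0001291.
- Standard error: √(0.0001291/10) = 0.00359. Difference over standard error: 0.0107/0.00359 = 2.98.
- Against t on 18 degrees of freedom (critical value 2.10), power is 0.804.

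The stated 80% is reproduced. The present point disputes no sample-size figure, but there is little power to spare.

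**What a valid test can detect.** For a facility-level mean with 10 facilities per arm, the smallest significant difference is 2.10 × √(2/10) = 0.94 between-facility standard deviations. Anything smaller goes unadjusted, however prognostic the covariate.

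**Chance selection with valid tests.** No threshold is stated, so 5% is assumed, with tests treated as independent. P(at least one selected) = 1 − 0.95ⁿ.

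- Ten listed factors: 1 − 0.95¹⁰ = 0.40, with 0.5 selected on average.
- Nine, leaving out infant sex: 1 − 0.95⁹ = 0.37.

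**If the tests ignored clustering.** The article does not say they would, so this is only a what-if. With 2000/20 = 100 women per facility and an assumed intracluster correlation (ICC), the design effect is DE = 1 + 99 × ICC. The false-selection rate is 2 × [1 − Φ(1.96/√DE)].

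| Assumed ICC | DE | Per covariate | At least one of ten |
|---|---|---|---|
| 0.01 | 1.99 | 0.165 | 0.835 |
| 0.02 | 2.98 | 0.256 | 0.948 |
| 0.05 | 5.95 | 0.422 | 0.996 |

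**Effect on power and type I error.** Simulation of a cluster-level analysis, 10 against 10, with one facility-level covariate whose correlation with the outcome is assumed. The effect was 1.3 standard deviations, giving unadjusted power of about 0.78 to 0.79; 15,000 runs per setting.

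| Correlation | Power, always adjusted | Power, stated rule | Type I error, always adjusted | Type I error, stated rule |
|---|---|---|---|---|
| 0.3 | 0.80 | 0.78 | 0.049 | 0.047 |
| 0.5 | 0.87 | 0.79 | 0.052 | 0.045 |
| 0.7 | 0.96 | 0.80 | 0.051 | 0.036 |

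The rule selected the covariate in about 5% of runs. In the other 95% the analysis was unadjusted, so nearly all the available gain was lost.

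**The case against.** The strongest reply is that the rule does little harm. It uses baseline data rather than outcomes, co-investigators see outcome data only pooled across arms during the trial, and an analysis plan not shown here could fix the candidate list and threshold. Much of this stands. Four stronger readings that a reader might infer are not supported:

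- **Inflated type I error.** The simulation shows none: 0.036 to 0.047 under the rule, slightly conservative. It used one covariate and a fixed rule, so it says nothing about discretionary choices, but the documents give no evidence of those either.
- **Chance selection in 84% to over 99% of trials.** That requires tests that ignore clustering, which the article does not state. Its primary and secondary models all carry facility and CHW random effects. Any relation between the stratification factors and the covariates would also lower these figures.
- **A chance-selection figure for mortality.** The ten factors come from in-depth questionnaires. Mortality comes from de-identified eCHIS records, and the candidate covariates there are not listed.
- **Infant sex and CHW workload as failures of the rule.** The questionnaire section does not call infant sex a baseline value. Workload is an exploratory outcome, outside a rule stated for primary and secondary outcomes.

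It can also be said that women are recruited after an unblinded allocation, so an imbalance may be more than chance. That is a reason to adjust for a fixed prognostic set. It does not rescue a significance filter, which passes over any imbalance short of significance.

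**Conclusion.** The point holds as one about precision and prespecification. The rule is fixed in advance, but the model is not: baseline tests settle it after allocation, in the hands of analysts who know the assignment. In the illustration it costs 0.08 of power at a correlation of 0.5 (0.87 against 0.79) and 0.16 at 0.7 (0.96 against 0.80). At 0.3 the loss is only about 0.01 to 0.02. Those correlations are assumptions, since the documents give none, and the simulation is a cluster-level simplification of the planned mixed models. The 37% to 40% chance of selecting at least one covariate applies to the in-depth cohort and assumes independent, valid 5% tests. No stated sample size or power figure changes.

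**What to change.** Delete the sentence. Before any comparative analysis, name a short fixed adjustment set for each primary and secondary outcome model, and state which model is primary.

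- **All models:** include the stratification factors in a form that 20 clusters can support, for example facility level and rural or urban designation. Eight stratum indicators would use 7 of the 18 between-facility degrees of freedom and leave 11. Facility level in three categories plus rural or urban would use 2 + 1 = 3 and leave 15.
- **In-depth cohort:** add a few baseline factors chosen on prognostic grounds by the trial team.
- **Mortality:** use only the stratification factors and covariates available in eCHIS. At the planning rates about 3240 × (0.0210 + 0.0103) = 101 deaths are expected after attrition, so the list must stay short.
- **Baseline table:** report balance descriptively, without tests.

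The cost is a wording change and a few between-facility degrees of freedom. No new data are needed.

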#### Interim analyses {21b}

An interim analysis for neonatal mortality will be performed using O’Brien-Fleming boundaries for benefit and harm when 50% of expected person time has been accrued. The study’s data safety monitoring board (DSMB) will meet to review the interim analysis and may conclude with recommendations to continue the trial without change, modify the trial, or terminate the trial.

#### Methods for additional analyses (e.g., subgroup analyses) {20b}

We have no pre-specified subgroup analyses.

#### Methods in the analysis to handle protocol non-adherence and any statistical methods to handle missing data {20c}

Based on the Mobile WACh NEO RCT [41], we expect a 10% loss to follow-up between enrollment and the 6-week study visit. We anticipate that women who are lost to follow-up are more likely to be disengaged from care and have experienced adverse outcomes. We also anticipate missingness may differ by arm, with the intervention arm having higher retention. A secondary analysis of mortality will be performed in which missing mortality at 28 days will be imputed using multiple imputations by chained equations (MICE).

To explore any dose–response effects associated with variation in the fidelity of intervention delivery, we will conduct an exploratory analysis comparing primary and secondary outcomes between participants who received low vs. high fidelity of the intervention, defined based on the number of automated and CHW messages received. Propensity score matching will be used to control for confounding by participant or CHW characteristics.

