**Fig. 2 Fig2:**
[figure not shown]
Intervention conceptual framework

Automated SMS topics and schedule are summarized in Fig. 3, based on the client’s gestational age, date of delivery, and delivery outcome, obtained from eCHIS. From enrolment until 38 weeks gestation, automated SMS are sent weekly, encouraging facility delivery and birth planning, and providing anticipatory guidance about neonatal danger signs and emotional support. From 38 weeks gestation until delivery, automated SMS are sent daily, with similar content and highlighting neonatal danger signs and ENC practices, including immediate and exclusive breastfeeding, thermal, and cord care. From delivery to 2 weeks postpartum, two messages are sent per day: one message with screening questions regarding neonatal danger signs and encouragement to message if they have a concern and one message with educational content on postpartum care and complications, ENC practices, and emotional support. From 2 to 6 weeks postpartum, SMS are delivered every other day. Additionally, based on input from perinatal clients, CHWs, and policymakers in formative design activities, clients receive a reminder message when they are referred to the healthcare facility by the CHW, when they are due for their 6-week postpartum facility visit, and when a CHW is scheduled to conduct a home visit. All messages open with the participant’s name, state that the message is from their CHW, and contain a question to engage women in conversation. Clients who deliver a preterm or low birthweight baby receive a modified track of messages, which includes information about additional care for small and preterm babies, including Kangaroo Mother Care. Clients who experience a stillbirth or neonatal death receive a 4-week curriculum of weekly bereavement messages which provide condolences and emotional support; messages related to the infant are stopped. The message bank is available upon request.

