#### Service delivery and implementation outcomes

In addition to clinical outcomes, we will compare service delivery outcomes between arms as exploratory outcomes (Table 1). These outcomes are ascertained from eCHIS data and self-report questionnaires from all CHWs (*N* = 700). These include home visit coverage (defined as number of home visits performed by CHWs); perinatal clinic referrals (defined as number of clinic referrals logged by CHWs in eCHIS for clients who are pregnant or up to 3 months postpartum); and CHW and supervisor workload (defined as time on all work duties, based on self-report questionnaire).

Within the intervention arm, CHV-NEO acceptability, adoption and fidelity of use by CHWs and their supervisors is determined using questionnaires and eCHIS data. Acceptability is defined as perception by CHWs that CHV-NEO is agreeable or satisfactory, using the AIM scale in CHW self-report questionnaire [48]; adoption is defined as the proportion of client SMS replied to by CHWs at all based on eCHIS data; and fidelity is defined as the proportion of client SMS responded to by CHWs in an appropriate and timely fashion, ascertained through monthly structured review and scoring of a sample of SMS conversations by clinically trained study team members. Quantitative data from CHW and supervisor questionnaires as well as qualitative interviews with CHWs and supervisors are used to define CHW-, supervisor-, and facility-level drivers of acceptability, adoption, and fidelity.

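### The exploratory dose–response analysis is fixed as a low versus high contrast of a message count, which cannot show the shape of a dose–response and may lose information

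*Protocol article*

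**What the plan says.** All of this is in the Protocol article. Item {20c} gives the aim, "To explore any dose–response effects associated with variation in the fidelity of intervention delivery, we will conduct an exploratory analysis", and the method, "comparing primary and secondary outcomes between participants who received low vs. high fidelity of the intervention, defined based on the number of automated and CHW". The count is of texts that each woman received. Confounding is handled as follows: "Propensity score matching will be used to control for confounding by participant or CHW characteristics".

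The article gives no cut-point and no expected distribution of counts. It describes no analysis of the count as a number or in ordered categories, and it does not name the control arm as a zero-dose group.

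The underlying count has a wide range. Under Intervention description {11a}, automated messages run weekly to 38 weeks, then daily to delivery. After birth, "From delivery to 2 weeks postpartum, two messages are sent per day", and then one every other day to 6 weeks. CHW replies to client texts come on top and have no schedule. Infant messages stop after a neonatal death.

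The section on service delivery and implementation outcomes uses the same word differently: "fidelity is defined as the proportion of client SMS responded to by CHWs in an appropriate and timely fashion".

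**The concern.** The method does not match the aim. A dose–response question asks whether the outcome changes steadily with exposure, flattens, or changes at some level. A two-group contrast gives one difference, which fits all three. It also treats women just either side of the cut as different, and women far apart on the same side as alike. If the effect is anything like linear, it wastes information that is already in the data.

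The two-group form is written into this document, so an analysis plan that follows it would inherit the problem wherever the cut is placed. The article describes no other analysis that links delivered messages to clinical outcomes.

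**Working it through.** **Inputs from the article.** In-depth cohort 2000, so about 1000 in the intervention arm and 900 after 10% attrition. Mortality cohort 7200, so 3600 per arm and 3240 after 10% attrition. Design rates 21.0 and 10.3 per 1000, coefficient of variation 0.25, 10 clusters per arm, two-sided α = 0.05 (Sample size {14}). Message schedule from {11a}.

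**Inputs assumed.** The shape of the dose distribution, the cut, and a linear effect. The article gives none of these.

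**1. The plan's own figure.** No power is stated for the dose–response analysis. The primary power does reproduce. With 360 × 0.9 = 324 per cluster, clusters per arm = 1 + (1.96 + 0.84)² × [(0.0210 + 0.0103)/324 + 0.25² × (0.0210² + 0.0103²)] / (0.0107)² = 9.97, so 10, with power 80.1%. The design assumptions can therefore be used for the event count: 3240 × 0.0103 ≈ 33 intervention-arm deaths.

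**2. Range of the count.** A woman starting at 28 weeks and delivering at 40 weeks is due 10 weekly + 14 daily + 28 twice-daily + 14 alternate-day = 66 automated messages. Delivery at 34 weeks gives 6 + 28 + 14 = 48. After a 40-week birth and a death on day 3, she has had 10 + 14 + 6 = 30 before any bereavement messages. The raw count thus depends partly on gestation and on the outcome.

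**3. Information kept by a split.** Let X be the dose and G the indicator of the high group. If the effect is linear in X, the share of information kept is ρ² = corr(X, G)². For a cut at the median m this is (E|X − m|)² / Var(X). Power that was 80% on the full scale becomes Φ(2.80ρ − 1.96).

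| Dose shape, median cut | ρ² | Loss | 80% power becomes | 900 women act like |
|---|---|---|---|---|
| Uniform | (1/4)²/(1/12) = 0.750 | 25% | 68% | 675 |
| Normal | 2/π = 0.637 | 36% | 61% | 573 |
| Exponential | (ln 2)² = 0.480 | 52% | 49% | 432 |

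**4. Sensitivity to shape and cut.**
- Quartile cuts lose about 44% (uniform) or 46% (normal).
- A very skewed lognormal dose (sigma 1) loses 56–87%, depending on the cut.
- A U-shaped dose cut at the median loses about 19%.
- With two separated clusters cut at the gap, the loss is simply the within-cluster share of the variance. With 30% of women around 10 messages (SD 8) and 70% around 70 (SD 15), a cut near the gap loses about 18%. A median cut on that same dose loses 32%.
- Other two-cluster doses with 20–50% of women in the low group, cut at the gap, lose 10–14%, so 80% power falls only to 74–76%.

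**5. The reverse case.** ρ² is symmetric. If the true effect is a step exactly at a median cut, the split is the efficient test. Where it has 80% power, a linear term would have 68%, 61% or 49% for the same three shapes.

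These are large-sample ratios without clustering or confounding. They compare two codings of the same exposure and do not forecast the power of the planned analysis.

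**The case against.** The strongest case against is that the size of the loss rests on things the article does not state. SMS needs client consent and can be stopped at any time, and automated messages follow a fixed timetable. Many women may therefore sit near none or near all of the messages, and a cut at the gap would then cost little. Linearity is the best case for a linear term, just as a step at the cut is the best case for the split. All of this stands, and it rules out any single figure for the loss.

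The cut-point, the number of categories and any accompanying trend model are details that a condensed article may leave to the analysis plan. That also stands, and their absence is not the complaint. The complaint is that the article does state a form, and that form has two groups.

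A reader might infer that this is the analysis meant to separate an ineffective intervention from an under-delivered one after a null result. The text does not support that. It calls the analysis exploratory and attaches no decision rule, alpha or power to it. Delivery is also assessed through the adoption and fidelity outcomes, the monthly message review and the interviews.

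Finally, the order of messages and outcome matters more for mortality than the cut does. Infant messages stop at death, so a more powerful test of a raw count would not give a better answer. This is accepted, and the fix allows for it.

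**Conclusion.** The point holds as a low-cost improvement to an exploratory analysis. A low versus high contrast cannot show a gradient, plateau or threshold, whatever the dose distribution.

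The information loss is conditional. With a roughly linear effect and a cut near the median, it is about 25% to 52% for uniform to exponential doses. It is nearer 10–19% for two clusters cut at the gap, and higher for very skewed doses. A reader might take a quarter to a half as an established loss, or conclude that keeping the count as a number always gives more power. Neither follows: the article gives no distribution or cut, and a true step at the cut would favour the split.

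Primary and secondary inference is unaffected.

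**What to change.** In item {20c}, make the main dose–response analysis a regression of each outcome on dose kept as a quantity, in the intervention arm, using the Table 1 mixed model with its facility and CHW random effects.

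- **Dose.** Measure automated messages as the share received of those due, which removes the dependence on gestation. Enter CHW messages as a separate term, because they have no schedule against which to take a share.
- **Mortality.** Count only messages up to a fixed time before the outcome, such as delivery.
- **Shape.** Use a linear term for the test. Check shape with a spline only for the common secondary outcomes; about 33 deaths will not support one for mortality.
- **Confounding.** Adjust directly for the same participant and CHW characteristics, or use continuous-exposure propensity weighting, in place of binary matching.
- **Low/high comparison.** Keep it as a descriptive or supporting analysis.

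The cost is a wording change and somewhat more analysis work, with no new data. The small downside is that a dose shape must be assumed.
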